**Intervention goals and details for HPI and the iDiet**

| iDiet (iDiet) | |
| --- | --- |
| Primary goals | - *Goals*: Weight loss (1-2 lb/week), dietary energy reduction (**approximately** 500-1000 kcal/week) consumed in regular meals, encourage activity (150 minutes/week). Please note individualized calorie goals are used per program specifications, ranging from 1000 to 2500 calories depending on the weight of the participant. The minimum calorie target recommended for our smallest people will be 1000 calories/day, which may not be as great as a 500 calorie deficit, and participants are able to request a different menu level if they wish. The goal for physical activity is also a broad goal. Participants will be provided with pedometers and forms for tracking pedometer counts and other activities. If participants tracked activity levels do not meet program goals, counselors will suggest incremental strategies to increase activity weekly through brisk walking, lifestyle activities or other exercise of the participant’s choice. Physical activity will be recommended starting after Session 3 and will be emphasized as an important factor for preventing weight regain once subjects are in maintenance. Participants will not be excluded or withdrawn from the study if they do not meet this recommendation. - *Core strategies*: Group classes, behavioral skills training and materials (e.g. pedometer, family-friendly menu examples and a log for self-monitoring weight) to support study adherance. |
| Nutrition goals and strategies | - *Goals*: High fiber (>40 g/d), moderately high protein (26% energy), low glycemic load (48% energy with low GI carbs) - *Core strategies*: Use of provided calorie- and nutrient-controlled menus and recipes. General portion guidelines and self-monitoring for portion sizes |
| Behavioral goals and strategies | - *Goals*: Hunger supression and maintenance of satiety; changing food preferences - *Core strategies*: Adherence to specific, repetitive provided menus and cognitive restructuring exercises. Frequent meals, use of free foods, optional portion size monitoring; raising self-efficacy, exercise |

| Human Performance Institute (HPI) | |
| --- | --- |
| Primary goals | - *Goals*: The primary training goal is to improve individual performance and increase quality of life by aligning participants’ direction in life with how and where they spend their energy.  The integrated training model states that increased life engagement leads to enhanced performance through focusing personal resources on a defined purpose or mission. The intervention is based on two foundational models: 1) the Energy Management Model and 2) the Change Process Model. The Energy Management Model focuses on four domains of energy which includes the spiritual, mental, emotional and physical areas of energy. The Change Process Model focuses on the elements of purpose, truth, and action to help participants indentify their purpose in life. - *Core strategies*: Group classes, exercise sessions, behavioral skills training and materials (e.g. exercise sessions, 360˚ energy profile and a 90-day training mission) to support study adherance. |
| Nutrition goals and strategies | - *Goals*: Help individuals understand the role that nutrition plays in energy management, engagement and performance, with a particular focus on maintaining stable blood glucose levels. Training participants that listening to one’s own hunger and satiety signals can lead to ideal energy, mood, performance, and body composition. - *Core strategies*: Focus on the glycemic index of foods and snacks, becoming more aware of meal timing, and understanding “five-handfuls” per meal (two handfuls of fruit, two handfuls of grain, and one handful of protein). |
| Behavioral goals and strategies | - *Goals*: To have individuals find and define a purpose or direction in life, in order to identify motivating factors that can help participants make difficult changes. The rationale is to tap into what is called “intrinsic motivation”, which, research shows, will facilitate more sustainable behavior change (68). - *Core strategies*: Workshops to discuss one’s purpose, facing the truth, working through setbacks, using training logs and acountability plans to help support study adherance. |

1. **Usual standard therapy vs solely for research purposes:** N/A
2. **Confidentiality of body measurements:** Please note we have no tissue banking. All anthropometrics will be done in a private area using a screen and necessary privacy measures including for recording and storing the collected data.
3. **Subject Timeline**:

**Table 1: Overview of Assessments and Assessment Schedule (in weeks):**

|  | **Intervention Worksites – HPI and iDiet Groups*** | **Control Worksites – Future HPI, and iDiet Groups*** |
| --- | --- | --- |
| **Measurements** |  |  |
| **Weight at site** | **0, 3, 6, 9, 12, 15, 18** | **0, 3, 6** |
| **Blood Pressure, Fasting lipid panel and Glucose** | **0, 6, 12, 18** | **0, 6** |
| **Waist and Hip Circumference** | **0, 6, 12, 18** | **0, 6** |
| **% Body fat** | **0, 3, 6, 12, 18** | **0, 3, 6** |

**Table 2: Overview of Questionnaires at Each Time point (in weeks):**

| **Questionnaires** | **Intervention Worksites – iDiet, and HPI Groups*** | **Control Worksites – Future iDiet, and HPI Groups*** |
| --- | --- | --- |
| **Demographics & Brief Medical History** | **0** | **0** |
| **Rand Quality of Life (SF-36)** | **0, 3, 6, 12, 18** | **0, 3, 6** |
| **IPAQ Physical Activity Questionnaire – Short form** | **0, 6, 12, 18** | **0, 6** |
| **Cravings Questionnaire** | **0, 6, 12, 18** | **0, 6** |
| **Three Factor Eating Questionnaire – R51** | **0, 6, 12, 18** | **0, 6** |
| **Food Preferences Questionnaire** | **0, 6, 12, 18** | **0, 6** |
| **MOS Sleep Questionnaire** | **0, 6, 12, 18** | **0, 6** |
| **Work Productivity and Impairment Scale (WPAI)** | **0, 6, 12, 18** | **0, 6** |
| **Ryff Purpose in Life Scale** | **0, 3, 6, 12, 18** | **0, 3, 6** |
| **Morningness Eveningness Questionnaire** | **0** | **0** |
| **Center for Epidemiologic Studies Depression Scale**  **(CES-D)** | **0, 6, 12, 18** | **0, 6** |
| **Profile of Mood States (POMs)** | **0, 6, 12, 18** | **0, 6** |
| **Cognitive Tests (computer based)** | **0, 6, 12, 18** | **0, 6, 12, 18** |

1. **Assessment of Participant Safety and Development of a Data and Safety Monitoring Plan (DSMP)**

A Data and Safety Monitoring Plan will be implemented to ensure the safety of the participants, as well as the validity and the integrity of the data. [name] with the help of the study physician and research coordinators will monitor all aspects of safety. A safety monitoring log will be developed and participants will be asked to record signs, symptoms and both serious and non-serious adverse events. Research assistants will be instructed to report any adverse events that occur during research activities to the PI as soon as possible. Both serious and non-serious events will be documented. An event will be considered serious if it results in death, is life-threatening, requires inpatient hospitalization, or results in a persistent or significant disability/incapacity, or might require medical or surgical intervention to prevent one of these outcomes. Non-serious events are defined as conditions that may be unpleasant to the participant, such as sore muscles, but do not require termination of participation. Any participant who experiences an adverse event has the option to continue participation in the study, if she so chooses and if it is safe and appropriate.

We do not consider excessive weight loss to be a risk because we do not anticipate this and will monitor for this as we have in our previous trials (34, 35). Further, the study physician will review the weight loss of individual participants on a quarterly basis. In the event that participants report symptoms or concerns about excess weight loss, or lightheadedness, intensive exercising, or if development of disordered eating is suspected, the study physician will review reports; he will then assess the participant by phone or in person to determine if appropriate referral to personal health care providers and/or exclusion from the trial is indicated. In the unlikely event that there are individuals whose BMI falls below 21.0 kg/m^2^ and still want to lose more weight, study physician will communicate by phone or in person to recommended no further weight loss. Individuals who do not comply with this recommendation will be excluded from further trial participation.

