The increase in vitality score in the intervention worksites compared to controls is expected to be 9 points at both time points compared to the control. Since randomization is at the worksite level, the total variance includes both the within worksite and between worksite variance. Based on a within worksite standard deviation of 15 and 20 people per worksite and a between worksite standard deviation of at most 3.4, 12 worksites with a 2:1 worksite allocation in favor of treatment are needed to have 80% power to detect an expected increase in vitality score of 9 points.

For the participants electing to participate in the behavioral weight loss program, randomization to either with provided Yevo foods or a gift card such that one half of the participants are in one group and the other half will be assigned to the remaining arm.. Assuming worksite is a fixed variable, 8 worksites with 30 subjects each (240 total subjects) is at least 80% powered to detect a 2.4% difference in weight loss with provided food compared to gift cards assuming no diet by food interaction. If there is a significant food by diet interaction, the study will have an 80% power to detect an interaction that is a 4.5% difference in weight change with provided food for iDiet and 3% improvement in diet.

Data analyses will be performed using the latest version of SAS for Windows, currently 9.4 (Cary, NC: SAS Institute Inc.). All testing will be two-sided and results will be judged statistically significant if the observed significance level (P value) is <0.05. Data will be examined graphically and numerically for outliers and other aberrations that might lead to misleading results. Data may be transformed prior to formal analysis if necessary to fit the assumptions for the statistical model to be employed. Both studies (HPI intervention and the iDiet intervention) will be analyzed according to Intention-To-Treat principles to best reflect what happens when individuals start one of the interventions. If necessary, missing data will be estimated using multiple imputations using the MI Procedure of SAS for Windows.

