We would like to note that there will be no exclusion of participants based on out of range blood values since the physician’s clearance form will serve as the reference document for inclusion in the study. Extreme values will be flagged and per the study physician’s recommendation participants will be sent a notification to see their primary care provider.

Non – English speaking participants will be excluded from participation as the proposed intervention programs and program related materials have yet to be translated into other languages and have yet to be designed or tested for non – English speaking populations. Furthermore we anticipate that since this is a worksite study most if not all employees will be English speaking

- - 1. Withdraw/Termination criteria: Participants will be withdrawn if they develop a condition that renders them ineligible after they sign consent including the period during which they are actively participating in the study. This includes women who self-report pregnancy, those whose health status changes affecting adherence to the diet, safety concerns for either the participant or the researchers, or outcome assessments (questionnaires) reveal that they have an exclusion criterion that they did not disclose at screening. Participants will be withdrawn from the study if they enroll in any other weight loss/intensive wellness program during the 18 month intervention. Furthermore the PIs with the consultation of the study physician may terminate or temporarily withdraw participants at their discretion if they feel that participant safety is of concern.

Participants may withdraw at any time for any reason. If participants decide that they wish to withdraw they will be provided a prorated stipend based on completion of study outcomes for the time point at which they withdraw and provided a stipend is identified at that time point.

If participants are deemed ineligible or withdraw at any time for any reason, any data collected up until this point in time will be retained throughout the duration of the study. We plan to discard this data 10 years after study completion. Retaining this data is necessary to report CONSORT chart details in any study publication(s).

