1. Physical risk: Minimal risk. Participants may experience some mild bruising or discomfort from the finger prick for the point of care assessments. The discomfort is normal and should dissipate. Excess weight loss may also be a potential risk if individuals continue to practice weight loss beyond the time period of the weight loss support group, but this is not recommended in the program. In addition, bloating, intestinal gas, or diarrhea has occasionally been reported with weight loss interventions as part of a change to a whole grain and higher-fiber diet. Participants in the HPI intervention may experience discomfort, during or following the exercise regimen that is provided as part of the training. Coaches will discontinue participants who report discomfort and it is anticipated that since participants have provided a physician’s clearance any discomfort following these sessions will be minimal and should be addressed with their primary care physician as needed. The Tanita Body Composition Analyzer is a scale with a bio-impedance analysis (BIA) function to measure body composition. To do this the device sends a very small charge through the body. The electric charge may interfere with electronic implanted devices. As a safety precaution, we will weigh participants with pacemakers or other implanted electronic devices using the weight-only feature of the scale. The BIA protocol and the data collection form include a question on use of pacemakers and other implanted electronic devices. Data collectors are instructed to elect the weight only feature to obtain weight for participants with these devices.
2. Psychological risk: The risk may be that no weight will be lost by some participants in the behavioral weight loss arms. Additionally, a potential risk is the discomfort associated with responding to questionnaires that may have sensitive information regarding weight and eating behavior.
3. Social risk: Knowledge of participation may not be completely confidential as there is a risk that coworkers are aware of employees who are enrollees in the wellness intervention programs. However, our experience is that the benefits (co-workers encouraging each other and other social support features) far out weight any potential risk and further we have not observed or have heard reports of negative effects.

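### The low-BMI safety rule removes participants from the trial rather than from the programme, so weight and safety follow-up stops for people excluded over a harm the protocol undertakes to monitor

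*Protocol*

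**What the plan says.** Under the physical risks, the Risk/benefit assessment says: "Excess weight loss may also be a potential risk if individuals continue to practice weight loss beyond the time period of the weight loss support". The section on participant safety and the DSMP takes a different line: "We do not consider excessive weight loss to be a risk because we do not anticipate this and will monitor for this". It then provides for a quarterly review of individual weight loss by the study physician.

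The DSMP section contains two routes out of the trial for this harm:

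- Symptoms or concerns about excess weight loss, or suspected disordered eating, lead to an assessment by the study physician "to determine if appropriate referral to personal health care providers and/or exclusion from the trial is indicated".
- For "individuals whose BMI falls below 21.0 kg/m^2^ and still want to lose more weight", the physician recommends no further loss, and then: "Individuals who do not comply with this recommendation will be excluded from further trial participation".

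On people who leave, the Withdraw/Termination criteria say that "any data collected up until this point in time will be retained throughout the duration of the study". They describe no assessment after that point.

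The Outcomes section makes weight change from baseline to 18 months primary for iDiet participants. The section on sample size and statistical analyses says both studies "will be analyzed according to Intention-To-Treat principles", with multiple imputation of missing data if necessary.

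**The concern.** Stopping an intervention and stopping follow-up are separate decisions, and this rule merges them. Being excluded depends on the harm itself and, in the iDiet arm, on the primary outcome variable.

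For safety, the trial loses sight of a participant once low BMI is confirmed and advice has failed, so it cannot report how those cases develop. For validity, later weights are missing because of how much weight was lost. If the two food groups differ in how often this happens, the comparison of provided food with gift cards is affected as well.

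**Working it through.** **What stops on exclusion.** Table 1 schedules weights at the intervention sites at 0, 3, 6, 9, 12, 15 and 18. Its title says weeks; I read these as months, in line with the Study Procedures section. Someone excluded after month 6 misses up to four scheduled weights (9, 12, 15 and 18), together with the quarterly weight review and the at-least-monthly adverse-event review. By then the provided food and gift cards have ended and the weekly iDiet classes have stopped, leaving roughly monthly meetings, online support and boosters. A late exclusion thus removes little intervention but all remaining scheduled measurement.

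**Whom the BMI rule can reach.** Loss needed to reach BMI 21.0 = (entry BMI − 21)/entry BMI. iDiet entry requires a BMI of at least 25.

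| Entry BMI | Loss needed to reach 21.0 |
|---|---|
| 25 | 16.0% |
| 26 | 19.2% |
| 27 | 22.2% |
| 28 | 25.0% |
| 30 | 30.0% |
| 40 | 47.5% |

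Any iDiet participant excluded under this rule has therefore lost more than 16% since screening. HPI entry is allowed from BMI 20, so an HPI participant can be below 21.0 after little or no loss. Weight is not primary in HPI, so only the safety part of the point applies there.

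**The plan's own yardstick.** The protocol states at least 80% power for a 2.4% difference with 240 iDiet participants, but gives no standard deviation, so the figure cannot be reproduced directly. Solving backwards with 120 per group and two-sided 5%: SD = 2.4/[(1.960 + 0.842) × √(2/120)] = 6.64 percentage points. I do not dispute this figure and use the 2.4 points only for scale.

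**Shift if only those still measured were analysed.** Assumed, not in the protocol: group of 120, mean loss 6%, excluded participants at 18% at month 18, all k of them in one group. Shift = k/(120 − k) × (18 − 6).

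| k | Shift (points) | Share of 2.4 |
|---|---|---|
| 1 | 12/119 = 0.10 | 4% |
| 3 | 36/117 = 0.31 | 13% |
| 5 | 60/115 = 0.52 | 22% |

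With mean losses of 4–8% and excluded losses of 17–25%, the range is 0.08–0.18 for one exclusion and 0.39–0.91 for five.

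**Shift with imputation.** Suppose later weight is imputed from earlier weights, with an assumed correlation ρ of 0.6–0.9 between earlier and 18-month loss and equal SDs. The remaining shift is (k/120) × (1 − ρ) × 12. For k = 1 this is 0.01–0.04 points; for k = 5 it is 0.05–0.20.

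**The case against.** The case against giving this much weight is substantial.

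- **The rule is narrow.** It needs a BMI below 21.0, a wish to lose more, contact from the physician and then non-compliance. Someone below 21.0 who accepts the advice stays in. The protocol calls the event unlikely. This stands.
- **The record before exclusion is kept.** With weights every three months, the large loss should normally be on file, so the missingness depends largely on observed weight, where imputation helps most. This stands in large part. The wish to go on losing is not a scheduled measurement, however, and imputation would assume a later course like that of similar participants who were not excluded for refusing to stop.
- **Other withdrawals also end participation**, for example for pregnancy or joining another programme. True, but those are not triggered by the primary outcome.
- **The end of safety follow-up is inferred from silence.** The physician will already have assessed or contacted the person, and serious-event reporting is not expressly limited to active participants. Fair, but exclusion from the trial with no later assessment described leaves staff no basis for continuing scheduled visits.
- **The two risk statements may be compatible.** The risk is placed after the support-group period, and iDiet meetings run about monthly to month 18, so that window may lie outside the trial. This softens the conflict, but the DSMP applies its monitoring and BMI rule during the trial, so the wording still needs aligning.

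A reader might infer more than the documents support:

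- That the largest weight losses leave the outcome. They do not: the cut is an absolute BMI, and a 30% loss from BMI 40 ends at 28.0 and stays in. The rule mainly reaches iDiet participants who entered at about BMI 25–28.
- That the rule contradicts intention-to-treat. It weakens it: participants remain in their randomised group, with retained data and imputation.
- That this is the only weight-loss harm named. Bloating, intestinal gas, diarrhea, lightheadedness and disordered eating also appear.

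**Conclusion.** The point holds in a limited form. Applied as written, the rule ends scheduled weights and safety reviews for a small number of people excluded over a harm that the protocol names and undertakes to monitor. That gap in safety follow-up is the main finding. It rests on reading exclusion from the trial together with the absence of any provision for later assessment.

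The statistical effect is secondary. In the iDiet arm the missing later weights are related to the outcome, but the bias is probably small: about 0.10 point per excluded person per 120 under the assumed 6% and 18% losses with a completer analysis, which the protocol does not plan, and about 0.01–0.04 with imputation under the assumed correlations. Placing every exclusion in one food group is a worst case that nothing in the protocol supports. No view is taken on the BMI threshold or on the clinical rule.

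**What to change.** Amend the DMSP wording without changing the BMI threshold or the physician's decision about programme participation:

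1. State that leaving the intervention does not by itself end follow-up. With the participant's agreement, and unless the study physician judges continued weighing inappropriate (relevant where disordered eating is suspected), the weights already scheduled in Table 1 and the adverse-event reviews continue to month 18.
2. Report these cases by randomised group and keep their weights in the intention-to-treat analysis.
3. Make the Withdraw/Termination criteria consistent with this.
4. Reconcile the Risk/benefit assessment and the DSMP section on whether excess weight loss is a study risk.

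The cost is a wording amendment, using visits, scales and reviews already planned, for a handful of people. The downside is that some excluded participants will decline further weighing, so the gap will shrink rather than close.
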